## Abstract

**Background:**

The aim of this study is to examine the feasibility of a future definitive randomised controlled trial of Family Focused Treatment for Adolescents UK (FFT-A UK) in the management of early-onset bipolar disorder (EOBD) (under 18 years). The FFT-A has been evaluated in the USA to augment the pharmacological treatment of adolescents with bipolar disorder (BD). The FFT-A UK has been condensed to 16 sessions over approximately 6 months to be utilised within the UK National Health Service.

Research from the USA suggests that families experience high levels of distress, stress, burden and family disharmony when living with a young person who has BD. The FFT-A UK is a family-based approach designed to increase understanding of BD (psycho-education), improve communication and increase ability to problem-solve.

**Methods/Design:**

The trial will examine the feasibility of a randomised, parallel group, non-blinded design and the procedures of a subsequent definitive trial. Thirty-three young people with BD and their families will be recruited. Participants will complete measures at baseline, on completion of the 6-month treatment and again after a further 6 months. The self-report measures include the Warwick Edinburgh Mental Well-being Scale, The McMaster Family Assessment Device (FAD), Conflict Behaviour Questionnaire aka ‘Interaction Behaviour Questionnaire’, EuroQuol EQ-5D-3L and EQ-5D-Y. Primary outcomes will be rates of eligibility, recruitment and retention, estimates of the variability in the self-report measures and assessment of the intervention delivery in the study population. Participants’ qualitative views on the measures and intervention will be sought to confirm the acceptability of intervention and study design. The health economics component will establish how cost-effectiveness will be assessed in a future definitive trial.

**Discussion:**

The study will produce a full trial protocol and amendments to the FFT-A UK to inform a well-designed multi-centre randomised controlled trial (RCT) as an adjunct to pharmacotherapy in the management of EOBD.

**Trial registration:**

Current Controlled Trials ISRCTN59769322

## Background

Bipolar disorder (BD) is a chronic remitting and relapsing mood disorder, characterised by mood swings from ‘lows’ (depression) to ‘highs’ (mania/hypomania) with periods of relative stability in between. It is most frequently diagnosed in young adults (20–30 years), but recent research has shown that the onset of symptoms can occur earlier. Early-onset BD (EOBD) often co-occurs with other mental health and developmental disorders making the diagnosis and management more difficult [1–3].

EOBD defined for this study as onset before 18 years of age is associated with high rates of impairment in emotional, cognitive and social development [4]. The National Institute for Health and Clinical Excellence (NICE) bipolar guidelines note that the involvement of families is important in the management of young people with EOBD and recommend psychological interventions over 6 months in combination with psychopharmacology [5].

There are a few evidence-based psychotherapeutic treatment options for EOBD. A number of psychological treatments used with adults with BD have been adapted for use with affected adolescents. These include Interpersonal and Social Rhythm Therapy [6], Dialectical Behavioural Therapy [7] and Cognitive Behavioural Therapy (CBT) [8, 9]. These treatments have been effective in research done in the USA and have shown to delay the recurrence of episodes, stabilise symptoms and improve medication adherence. Other researchers have tailored therapy to include the family in conjunction with the young person. This research has shown that family-focused CBT is effective in treating children aged between 7 and 13 years with BD [10]. Furthermore, recent research has suggested that reducing parent stress and improving family functioning may be the most potent ingredient of the treatment [11]. Fristad and colleagues [12] have shown that a multi-family psycho-education group method is effective in improving symptoms and social and family functioning. [name] et al. have adapted their manual-based family treatment for adults for use with adolescents (FFT-A) [13]. The results of a 2-year randomised controlled trial showed that those adolescents who received the 9-month, 21-session intervention had a more favourable and rapid recovery from their index depressive episode than patients in enhanced care (mean 10.2 weeks, 95 % CI 1.04–3.29, *p* = 0.04) [13]. A further study showed that FFT-A had a stronger effect for those who live in families with high emotional stress levels whereby adolescents with BD in high expressed emotion families showed greater reductions in both depressive and manic symptoms [14]. A more recent study showed that FFT-A together with pharmacotherapy proved no more effective than pharmacotherapy with brief psychotherapy in speeding up recovery or delaying recurrence of BD in adolescents. However, FFT-A was more effective than brief psychotherapy in reducing the severity of manic symptoms in year 2 [*F*(8,742) = 1.98, *p* = 0.046] [15].

BD affects not only the patient but also their family. Family-based interventions may therefore offer advantages in the long-term management of this disorder. One study has reported that there are high levels of stress in parents of youths with BD [16]. Reinares and colleagues [17] showed that a psycho-education family intervention reduced the distress and subjective burden and the caregiver’s belief about the link between the objective burden and the patient. Other studies in families with BD children acknowledged significantly more minor conflicts with family members than either unipolar or control group families [18]. Belardinelli et al. [19] found that the family environment of bipolar children in comparison to healthy children showed greater levels of dysfunction as measured by the Family Environment Scales. Parents of children with BD reported lower levels of family cohesion (*p* < 0.001), expressiveness (*p* = 0.005), active-recreational orientation (*p* < 0.001), intellectual-cultural orientation (*p* = 0.04) and higher levels of conflict (*p* < 0.001) than parents with no bipolar children. Furthermore, a study reported higher levels of conflict (*z*=4.729, *p* < 0.0001) on the Family Environment Scales in families where one parent had BD than families where neither parent has BD [20]. That family functioning is important in the prognostic outcome of EOBD has been demonstrated in a study that showed decreased family problem solving ability, as measured by the Family Assessment Device (FAD), predicted increased persistence of adolescents’ depressive symptoms [21]. The psychotherapeutic studies for EOBD to date have been undertaken in the USA. Given the differences in the health care systems between the USA and the UK, it is important to evaluate the effectiveness (including the cost-effectiveness) of psychotherapeutic evaluations for EOBD in the UK. This study intends to examine mental well-being and impact on family functioning along with quality of life adjusted years (QALYs).

### Aim

The aim of this study is to examine the feasibility of a future randomised controlled trial (RCT) of family-focused treatment (FFT-A UK) in the management of EOBD. The FFT-A was first adapted from the FFT in the USA to treat young people with BD and their families. The FFT-A UK version is further adapted from the original. These adaptations include some textual changes to make the version more relevant to UK culture (e.g. Coach replaced with Therapist) along with being condensed into 16 sessions taking place over 6 months (as opposed to the existing FFT-A version at the time of 21 sessions taking place over 9 months).

The study will investigate the acceptability of the FFT-A UK and explore issues of eligibility, randomisation, recruitment and retention rates and variability in the proposed outcome measures to inform the design of a multi-centre RCT with long-term follow-up.

The specific objectives of this feasibility trial are:Is it feasible to deliver the FFT-A UK to young people (under 18 years) and their families?What are the likely consent, eligibility and retention rates as well as the acceptability of being randomised to a delayed treatment arm?What are service users and their family’s views about taking part in a RCT and completing the study assessments and outcome measures?What is the variability in the outcome measures?

The results of this feasibility study will inform the development of a definitive multi-centre RCT to evaluate the clinical and cost-effectiveness of FFT-A UK as an adjunct to pharmacotherapy in the management of EOBD. Our hypothesis for the definitive RCT will be that the addition of a family-focused psycho-educational treatment will be more effective and cost-effective in the management of EOBD than treatment as usual (TAU) defined as review appointments every 3–6 months with their Consultant Psychiatrist.

## Methods/Design

### Design

The feasibility trial of a modified version of the FFT-A will examine the design and procedures for a subsequent definitive trial of the FFT-A UK for use in UK community-based settings. This is a mixed methods feasibility study with two components:A single-centre, open randomised controlled trial of FFT-A UK in the management of EOBD compared to treatment as usual. The primary outcome measures are rates of recruitment, randomisation and data completion. We will also investigate the variability in the validated questionnaires to determine the best measures to use in a future definitive trial.Qualitative interviews of a purposively sampled sub-set of families eligible for the feasibility trial to explore willingness to participate, be randomised and explore overall trial experience. An attempt will be made to undertake qualitative assessments with families who did not consent to be randomised.

### Participants

Thirty-three (to allow for a 10 % attrition rate) young people with a clinical diagnosis of EOBD and their families will be recruited into this trial.

### Inclusion criteria

Confirmation of diagnosis of BD and currently in remission using the WASH U KSADS (Washington University at St. Louis Kiddie Schedule for Affective Disorders and Schizophrenia) [22]Fluent in the English languageTypically developing with ability in the average range and able to engage in psychotherapy (i.e. attending or having attended mainstream school)Age between 11 and 18 years

### Exclusion criteria

Not meeting criteria for a diagnosis of BD according to the WASH U KSADSCurrently unwell in an episode of bipolar disorder (e.g. mania/hypomania/depression/mixed episode)Lack of fluency in the English language that might prevent engagement in psychotherapyLow intellectual functioning that might not allow young people to engage in the FFT-A UK

### Recruitment

Referrals were made through:The National Tertiary Adolescent Bipolar Service, Northumberland Tyne and Wear NHS Foundation Trust.Consultant Child and Adolescent Psychiatrists within Child and Adolescent Mental Health Services (CAMHS) in North East England. With the permission of the treating Consultant Child and Adolescent Psychiatrist, a Clinical Studies Officer (CSO) from the Clinical Research Network (CRN) will search patient records electronically and inform the clinician of potential participant families.Advertising this study in the North East England with Bipolar UK, via their newsletter, ‘Pendulum’. Potential participants will be asked to contact their clinically responsible Consultant Child and Adolescent Psychiatrist to discuss the research project.

### Consent component 1

The referring Consultant Psychiatrist will give the young person and their family the Study Information Pack (SIP). The SIP will consist of information sheets for the young person, parents/carer and an Expression of Interest (EOI) form. The clinician will ask the family if he/she can forward their contact details to the research team so that they can ask more questions about the study before making a decision about giving written informed consent. Alternatively, using the contact information (email, telephone and/or post) on the EOI form, the research team can contact the young people and their families directly. Potential participants will be given at least 48 h to read the information sheets before the consent visit will take place. The research team will then request a CSO from the North East and North Cumbria CRN to set up a mutually convenient time and venue to meet with the young person and his/her family to further discuss this project in detail. Those wishing to take part are asked to provide written informed consent by initialling, signing and dating a study consent form which is witnessed by the CSO who has documented delegated responsibility to do so. Written informed consent is always obtained before any study-specific procedures including eligibility assessments and the collection of baseline data take place. Informed consent and assent are taken as appropriate. The original signed consent/assent forms are retained in the investigator site file with a copy retained in the clinical notes and another copy provided to the participant and family. Those families who decline to take part will be asked if they would like to give their reasons, though the right to refuse to participate without giving reasons is respected. After consent and assent, the eligibility assessments will be undertaken during a separate appointment.

### Consent component 2—qualitative interviews

Upon completion of the FFT-A UK, patients and their families will be invited to take part in the qualitative part of the study. They will be asked to comment about the treatment programme, fill out questionnaires, be randomised, etc. Information sheets will be given to families at the end of the final treatment session. After a minimum of 48 h, the research team will then request a CSO from the North East and North Cumbria CRN to set up a mutually convenient time and venue to meet with the young person and his/her family to further discuss this aspect of the project in detail. Those wishing to take part are asked to provide written informed consent by initialling, signing and dating a study consent form, which is witnessed by the CSO who has documented delegated responsibility to do so. Those consenting will be contacted by a member of the research team to discuss a suitable date, time and venue for the interview.

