### Interventions

#### Control condition: delayed treatment with treatment as usual

Families and the young person with bipolar disorder will receive usual care delivered by their referring Consultant Child and Adolescent Psychiatrist and the CAMHS team (usually a review appointment every 3–6 months). Families and young people will be offered the intervention after 1 year when all trial data collection is completed.

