### Qualitative data and analysis

Semi-structured interviews with young people and family members in the trial will be employed to gather their individual views in detail, while a focus group will allow trial participants to feed back on the findings from the individual interviews, and provide socially constructed perspectives to contrast with individual ones. Employing both methods will enable the participation of both those who may feel inhibited by group discussion and those unable or unwilling to attend interviews.

We will purposively sample families (*n* = 15), including three families in the control condition, seeking a representative male/female ratio and diversity in terms of age, diagnosis and time since diagnosis, family members and size. An attempt will be made to interview 2 family members within each family either face to face at the University, at home or by telephone by a qualitative researcher, giving a sample of 30 participants. Interviews will commence after 6 months following the last session of the intervention, with each interview expected to last approximately 45 min. Since it will also be important to feasibility to know why families may not wish to take part in the intervention or research, we will also invite a member from each of 5 families refusing participation to consent to a brief telephone interview on a voluntary basis to raise concerns they may have had. The interview agendas will initially be developed by members of the Project Advisory Group (PAG) including our parent and young people representatives to cover areas of research interest (attitudes towards and experiences of both the intervention and research procedures). The agenda will be flexible to allow both expected and emergent themes to be incorporated into later interviews [37].

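### The written interview invitation depends on finishing therapy: it misses immediate-arm families who stop early and does not fit the three control families the plan wants to interview

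*Protocol article*

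**What the plan says.** Four parts of the protocol article bear on who is interviewed and when.

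- **Consent component 2 (qualitative interviews)** sets the invitation point: "Upon completion of the FFT-A UK, patients and their families will be invited to take part in the qualitative part of the study". The sheets are handed over then: "Information sheets will be given to families at the end of the final treatment session".
- **Qualitative data and analysis** sets the sample: "We will purposively sample families (*n* = 15), including three families in the control condition". It also sets the timing: "Interviews will commence after 6 months following the last session of the intervention". Outside the 15, it adds a group who declined the trial: "we will also invite a member from each of 5 families refusing participation to consent to a brief telephone interview".
- **Control condition** says when the delayed arm meets the therapy: "Families and young people will be offered the intervention after 1 year when all trial data collection is completed".
- **Aim** lists among the objectives the "acceptability of being randomised to a delayed treatment arm".

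The Design section describes the interview frame more broadly, as a purposive subset of families eligible for the trial. No section gives an invitation point for a family that leaves therapy early, or for a control family during its control year.

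**The concern.** An invitation triggered by finishing a treatment selects on an outcome of that treatment. Families who find FFT-A UK unacceptable are more likely to stop before session 16, and a family that stops never reaches the session at which the sheet is given. The article relies on qualitative views to confirm that the intervention is acceptable and to shape its adaptation for a definitive trial. If the treated families interviewed are all finishers, their account will lean favourable.

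The same trigger does not work for the delayed arm. The sampling plan asks for families in the control condition, but the consent section ties their invitation to an event that does not occur while they are in it. Staff would have to improvise a consent route that the article does not contain, for the families with direct experience of the delay named in the objectives.

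**Working it through.** **The plan's own numbers.** The recruitment target is 33, to allow for 10% attrition around 30. 30 × 1.10 = 33 gives the stated figure (30 / 0.90 = 33.3, rounded up, would be 34; the difference does not matter here). The number to approach is 33 / (2/3) = 49.5, or 50, as stated. The therapy outline adds up: 7 + 4 + 4 + 1 = 16 sessions, and 7 + 4 × 2 + 4 × 2 + 2 = 25 weeks, counting two weeks for the final overview session.

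**Families missed in the immediate arm.** Inputs: 33 families (Participants), 1:1 allocation (Randomisation), 10% attrition (Participants; Sample size considerations cites less than 10% in the therapy phase of a similar study). The arm holds 33 / 2 = 16.5, so 16 or 17 families. With early-stopping proportion d and arm size n, expected early leavers are n × d and the chance of at least one is 1 − (1 − d)^n. Rates other than 10% are assumptions, shown for range.

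| d | Expected early leavers (n = 16 to 17) | Chance of at least one |
|---|---|---|
| 5% | 0.8 to 0.9 | 56 to 58% |
| 10% | 1.6 to 1.7 | 81 to 83% |
| 20% | 3.2 to 3.4 | 97 to 98% |
| 30% | 4.8 to 5.1 | above 99% |

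At 10%, 14.4 to 15.3 families finish. The plan needs 15 − 3 = 12 treated families, which is 12 / 15.3 = 78% to 12 / 14.4 = 83% of the finishers. Interviews would therefore cover most finishers and, by the written route, none of the early leavers.

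The number missing the trigger could exceed the formal dropouts. The article counts a family as a dropout only if it says it no longer wishes to continue. A family whose therapy is suspended and never resumed would also miss the final session.

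**The control families, passages side by side.**

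1. Consent component 2: the sheet is given at the final treatment session.
2. Control condition: therapy is offered after 1 year, once trial data collection is complete.
3. From 1 and 2, a family still in the control condition has had no final session and so has no invitation point.
4. Qualitative data and analysis: three control-condition families are to be interviewed, with timing counted from the last session, which such a family does not have.

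Statements 1, 2 and 4 cannot all be followed. Using the trigger after the delayed therapy would reach the family only once it had been treated, when it no longer speaks as a control.

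**Whether other sources fill the gap.** The five refusing families never had therapy and cannot say why someone stopped it. The focus group is built around a presentation of findings from the interviews. Attendance and retention records count those who leave but do not give their reasons. The listed sampling dimensions (sex, age, diagnosis, time since diagnosis, family members and size) do not include therapy completion.

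**The case against.** The best reply is that this is a condensed article. It does not call the final-session handover the sole route, it nowhere excludes early leavers, and its Design section draws the sample from eligible families. Consent logistics for subgroups may sit in the full protocol. This stands in part: missing an early leaver follows from the written procedure and is not a stated exclusion. But the article does not merely leave the matter out. It states a trigger, and that trigger conflicts with its own sampling plan and with the timing of delayed therapy.

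Three stronger readings are tempting, and the documents do not support them.

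- *Control families will not be heard.* The sampling plan includes three of them. What is missing is a workable way to invite them.
- *Acceptability as a whole rests on completers.* Interviewed families in either arm are asked about being randomised, five refusing families are sought, decliners may give reasons, and retention and attendance are recorded. The selection affects only interview views of the therapy among treated families.
- *Control interviews would fall so late that only early-recruited controls could be reached.* This applies the trigger to therapy given after trial data collection, although the plan samples families in the control condition. The interview timing can also be read as following the 6-month course, and the article does not say when the 36 months began.

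The scale objection also stands: at the stated attrition one or two families are affected, and some who have said they no longer wish to continue may decline an interview.

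**Conclusion.** The point holds as a conflict between the consent route, the timing of delayed therapy and the sampling plan, and as selection of completers in the interview evidence on the therapy. The selection concerns about 1.6 to 1.7 of 16 to 17 immediate-arm families, with an 81 to 83% chance that at least one exists. This assumes that the 10% attrition applies to therapy in this arm and that families leave independently. The conflict affects all three planned control families. It should be corrected because the interviews are meant to inform the therapy and design of the definitive trial and the correction is cheap. It does not undermine the feasibility rates or the estimates of variability.

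**What to change.** Keep the 15 families and the three controls, and reconcile Consent component 2, Control condition, and Qualitative data and analysis as follows.

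- **Immediate arm:** give the information sheet at the final session or when therapy stops for any reason, whichever comes first. State when a suspended course counts as stopped for this purpose.
- **Delayed arm:** give the sheet at T12, before any FFT-A UK session, and time control interviews from T12.
- **Sampling:** add therapy completion status to the purposive dimensions, so that early leavers are sought where they exist.

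A fixed quota for early leavers is not advised. At 10% attrition, the chance that three or more exist among 16 to 17 families is only about 21 to 24% (binomial). Nor does the article show that three control families are too few.

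The cost is a minor amendment to the consent pathway and sampling description, with no extra interviews and possibly one or two fewer places for completers.
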